### Brain imaging in NPH

Magnetic resonance imaging (MRI) is the preferred modality for assessment of NPH
^
25
^. The classical imaging finding of NPH is enlargement of the ventricles (‘ventriculomegaly’), frequently operationalised as a raised Evans’ Index (EI)
^
26
^. However, this measure varies widely between individuals, is non-specific, and is elevated in a significant proportion (29%) of healthy elderly aged 65–84 years
^
27
^. EI increases with age and with male sex
^
27
^. The presence of disproportionately enlarged subarachnoid space hydrocephalus (DESH), characterised by tight high convexity sulci, enlargement of the Sylvian fissures, and ventriculomegaly, supports the diagnosis of NPH according to guidelines
^
6
^ and predicts response to treatment
^
28
^. In addition, an acute angle at the corpus callosum, widening of the temporal horns, white matter hyperintensities (WMHs), focal bulging of the roof of the lateral ventricles, and focal enlargement of sulci are seen in NPH. These imaging features are indirect markers of communicating hydrocephalus but do not confirm a specific underlying pathophysiological process, and therefore serve as potential indicators rather than definitive signs of NPH. Kockum’s RadScale
^
29
^ is a validated radiological scale incorporating these features that is used to aid pre-operative assessment of possible NPH cases.

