## Aims and objectives

In this proposal, we aim to investigate the clinical and imaging features of NPH in a memory clinic population. To do this, we will determine the period prevalence of recorded diagnosis and radiological features of NPH in memory services and describe their association with demographic characteristics, risk factors, symptoms, and outcomes, using linked free text notes, hospitalisation, brain imaging, and mortality data. We will evaluate automated tools for measuring CA and other imaging markers on routinely collected brain MRI scans and examine their clinical utility as biomarkers for NPH in this setting. In this memory clinic cohort study, we hypothesise that imaging features of NPH will predict NPH diagnosis. We hypothesise that CA will be smaller among people with a diagnosis of NPH compared to individuals diagnosed with dementia and its subtypes, taking into consideration the caveat that people with NPH may not have a formal diagnosis.

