### Study design

We will assemble a retrospective cohort study using SLaM’s CRIS data platform. The study population will be all people aged 60 years and above with at least one referral to memory services recorded over the study period 2007–2024. We expect at least 20,000 participants in this cohort. We will extract relevant anonymised retrospective patient data from CRIS for the entirety of the cohort and specify the data extraction date. We will examine CRIS data and use linkage data to HES, ONS, and imaging data.

A subset of this cohort will have linked T1-w, T2-w, and FLAIR brain MRI scans that have been collected as part of routine clinical care over the period 2008–2021. We expect to have at least 5,000 people in this sample, based on the number of scans currently available, however the sample size is subject to change as these datasets are live.

*Inclusion criteria:*

Aged at least 60 years at time of memory clinic referralReferral to memory services, recorded in CRISPeople who are referred but do not attend a review will be included and compared with those who do attend, though they may have limited data

*Exclusion criteria:*

Nil

*Cohort entry date:*

Date of referral to memory service

*Exit from cohort:* Censored at minimum of

DeathIncident NPH diagnosisEnd of study period

*Covariate assessment window:*

Anytime prior to cohort entry date up to three months after date of first face-to-face or virtual review in memory clinic, inclusive

*Primary outcome:* ICD10 code G91.2 recorded in CRIS
*or* HES
*or* ONS,
*or* context-confirmed NPH recorded in CRIS

*Possible secondary outcomes:*

MortalityHospitalisation profileDementia diagnosisCognitive trajectorySymptoms of NPH (eg. falls)

*Exposures:*

CA in degreesVentricular volume in mm
^3^
White matter hyperintensities (WMH) volumesOther brain measures to be determined (TBD)

*Possible covariates:*

AgeSexEthnicityIMDRisk factors for NPHCognitionHealth of the Nation Outcome Score (HoNOS)

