### Descriptive analyses

We will calculate the period prevalence of recorded diagnoses of NPH in our sample, as defined in
Table 2. We will define NPH diagnosis as ICD10 code G91.2 recorded in CRIS or HES or ONS, or context-confirmed NPH recorded in CRIS.

We will describe the distribution of imaging features of NPH in this population and produce summary statistics. This will include examining for normality and calculating the mean or median of these measures in the population. We will visualise the data and categorise the data into quartiles or quintiles, where appropriate. We will take a dimensional approach, considering these measures as continuous and categorical variables.

We will examine the association between CA and other brain measures of NPH. We will examine the association between imaging features of NPH and markers of neurodegeneration, such as cortical atrophy and hippocampal volume. We will describe the period prevalence of imaging features suggestive of NPH, based on reported cut-offs.

We will describe variation in CA and other imaging features of NPH according to demographics, covariates, and risk factors for NPH (see
Table 2).

We will describe imaging features of NPH in relation to recorded diagnosis of NPH. We will describe the relationship between imaging features and diagnosis of NPH, including whether a clinically useful threshold exists. We will build several models to examine individual imaging features of NPH and combinations of features, to assess for possible additive effects of these. In addition, we will compare clinical radiological reports, which are available in the free text notes of CRIS, with imaging features of NPH to look for concordance of these findings and to determine what role the imaging report played in future management of these cases.

We will examine for systematic differences based on EHR data between individuals with and without imaging data in the cohort using logistic regression.

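### Imaging-feature prevalence is aimed at memory services but estimated only in the quarter or so with a linked MRI, and the planned selection model is not carried into the estimate

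*Protocol article*

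**What the plan says.** Under Aims and objectives, the protocol article states: "we will determine the period prevalence of recorded diagnosis and radiological features of NPH in memory services". Study design defines that population as people aged 60 or over with "at least one referral to memory services recorded over the study period 2007–2024", and keeps those who were referred but never attended. On size it says "We expect at least 20,000 participants in this cohort".

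Imaging features exist only for a subset. Study design describes the scans as "collected as part of routine clinical care over the period 2008–2021" and says "We expect to have at least 5,000 people in this sample".

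Descriptive analyses gives the estimate: "We will describe the period prevalence of imaging features suggestive of NPH, based on reported cut-offs". The same section plans one check on selection: "We will examine for systematic differences based on EHR data between individuals with and without imaging data in the cohort using logistic regression". Strengths and limitations adds that groups will be compared for systematic bias. It counts it as a strength that scans were requested on clinical grounds at one imaging centre. No section says what will be done if scanned and unscanned people differ.

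**The concern.** The population named in the aim and the population that supplies the data are not the same. A frequency observed in scanned people equals the frequency in the service only if having an MRI is unrelated to the imaging features, given whatever is adjusted for. The protocol gives reasons to doubt this. Brain imaging in NPH says "Magnetic resonance imaging (MRI) is the preferred modality for assessment of NPH", and the scans were requested for clinical reasons. The introduction links NPH to older age, and Evans' Index to age and male sex. If MRI use varies with age or with suspicion of NPH, feature frequency may differ between scanned and unscanned people.

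Several outputs depend on this: the imaging prevalence and distributions (the introduction treats normative data as key to screening tools), the claim to give a first figure for NPH that UK memory clinics may have missed, and the predictive values planned under Diagnostic accuracy of CA, which move with prevalence. A table of differences tells readers that the scanned group is unusual. It does not tell them how far the prevalence is off.

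**Working it through.** The protocol gives no figure or precision target for imaging-feature prevalence, so there is nothing of its own to reproduce first. The check has four steps.

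**1. Coverage**
- Share with MRI: 5,000 / 20,000 = 25%. Both counts are stated as minimum expectations, so this is approximate.
- Years: scans cover 2008–2021 (14 calendar years) and the cohort 2007–2024 (18).
- Non-attenders are in the cohort and may have little chance of a linked scan.

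**2. Expected frequency among scanned people**
- Inputs from the Table 3 caption: NPH prevalence about 1%, sensitivity 97%, specificity 88% at a callosal angle below 90 degrees.
- Frequency = 0.01 × 0.97 + 0.99 × 0.12 = 0.0097 + 0.1188 = 0.1285, or 12.9%.
- The caption inputs are used because the two column totals in the table (50 and 4,850) add to 4,900, not 5,000. The printed cells give the same answer: 631 / 4,900 = 12.9%.
- Sampling half-width at n = 5,000: 1.96 × √(0.1285 × 0.8715 / 5,000) = 0.0093, about 0.9 percentage points.

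**3. What the cohort figure could be**
Let r be the frequency in unscanned people divided by that in scanned people. The document gives no value for r; those below are assumptions.
- Cohort frequency = 0.1285 × (0.25 + 0.75 × r).
- r = 0.5: 8.0%
- r = 0.75: 10.4%
- r = 1: 12.9%
- r = 1.25: 15.3%
- r = 1.5: 17.7%
- With no assumption about unscanned people: from 0.25 × 0.1285 = 3.2% to 0.0321 + 0.75 = 78.2%.

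At r = 0.75 or 1.25 the shift is 2.4 points, more than twice the sampling half-width. A confidence interval from the scanned group would not convey it.

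**4. Predictive values**
Apply the same range of r to NPH itself (a separate assumption), with 1% among scanned people and sensitivity and specificity held at 97% and 88%.
- PPV at 1%: 0.0097 / 0.1285 = 7.5%.
- r = 0.75: cohort prevalence 0.01 × 0.8125 = 0.8125%; PPV = 0.00788 / (0.00788 + 0.11903) = 6.2%.
- r = 1.25: cohort prevalence 0.01 × 1.1875 = 1.1875%; PPV = 0.01152 / (0.01152 + 0.11858) = 8.9%.
- NPV stays above 99.9% throughout, so here the choice of prevalence matters mainly for the PPV.

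**The case against.** The strongest reply is that this is a condensed article for a study described as mainly descriptive and exploratory. It states openly that scans exist for a subset, plans a model of who has imaging, acknowledges that clinician-led data may be biased, and leaves room for further analyses. A separate analysis plan could add weights. The primary outcome, recorded NPH, needs no scan and is measured in the whole cohort.

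Much of this stands. That the estimate will be unweighted is read from silence, since no weighting is named anywhere. The imaging prevalence is one descriptive output and not the primary result. Table 3 applies its 1% to the scanned people and claims nothing about the whole cohort.

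A reader might go further and infer that the bias has a known sign, for example because younger people are scanned more often or because suspected NPH triggers MRI. The documents do not support that. They give no MRI rates by age and no callosal angle by age. Naming MRI as the preferred modality does not show that suspicion of NPH drove scanning in these services.

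It is also fair to say that careless weighting could do harm. If age and suspicion of NPH pulled in opposite directions, weights that corrected for age alone could leave a larger net error than no weights. Non-attenders with almost no chance of a scan cannot be represented by weighting at all.

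What does not stand is the argument that similar selection by clinical need settles the matter. It supports comparisons among scanned people, not their representativeness of all referrals. Nor is the mismatch a detail left for later: the whole-service target, the scanned-only estimate and the check without a consequence are all in the protocol text.

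**Conclusion.** The point holds in a limited form. As written, the plan would attribute to memory services a frequency that applies to people with a linked MRI, about a quarter of the cohort, and its only response to selection is to describe it. The estimate may be biased for the service in an unknown direction. The size cannot be derived from the document. The range of 10.4% to 15.3% around 12.9% rests on the Table 3 inputs and on an assumed ratio of 0.75 to 1.25; it shows only that modest selection would outweigh the sampling error of about 0.9 points. The scanned data remain valid for scanned people, and whole-cohort recorded NPH prevalence is untouched. This is a worthwhile and cheap improvement, not a flaw that undermines the study.

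**What to change.** - Word the unweighted imaging prevalence, distributions, PPV and NPV as applying to people with a linked MRI.
- Beside them, report estimates weighted by the inverse probability of MRI, taken from the imaging model already planned. Restrict these to people who attended and were referred in the years that scans cover, and name that group as the target.
- Include as predictors age, sex, ethnicity, IMD, service, year, cognition, comorbidity and NPH symptoms (falls, bradykinesia, incontinence) recorded before the scan. The Table 2 symptom variable also counts symptoms after the index date, so it needs a time limit here, with an equivalent date for unscanned people.
- Report recorded-NPH prevalence separately for scanned and unscanned people. Read it with care, because a scan may itself lead to the diagnosis.
- Give PPV and NPV at both the scanned and the whole-cohort prevalence, stating that the latter assumes the same sensitivity and specificity in unscanned people.

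The cost is modest extra analysis with a model and variables that are mostly planned already. Intervals will be wider, and bias from unmeasured reasons for MRI will remain. The change of wording costs nothing and should be made even if the weighting is not.

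### The imaged versus non-imaged comparison spans referrals from 2007–2024 while scans cover only 2008–2021, so it mixes archive coverage with clinical selection into MRI

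*Protocol article*

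**What the plan says.** The Study design section defines the cohort as people aged 60 or over "with at least one referral to memory services recorded over the study period 2007–2024", with entry at "Date of referral to memory service". Follow-up ends at death, incident NPH or the end of the study period. On size it says "We expect at least 20,000 participants in this cohort".

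The imaging subset has scans "collected as part of routine clinical care over the period 2008–2021". On its size the section says "We expect to have at least 5,000 people in this sample", and adds that "the sample size is subject to change as these datasets are live". No later end date for the scans is given.

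The Descriptive analyses section sets the comparison: "We will examine for systematic differences based on EHR data between individuals with and without imaging data in the cohort using logistic regression". It names no referral window and no model terms. The list of possible covariates in Study design contains neither referral year nor length of follow-up.

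Timing differs between variables:
- Study design closes the covariate window three months after the first review. In Table 2 the risk factors close three months after the index date, and the cognitive scores, HoNOS and recorded diagnoses are taken at or nearest to it.
- Table 2 defines NPH symptoms and depression as ever recorded, including any time after index, and gives NPH diagnosis no time limit.

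**The concern.** A comparison of imaged with non-imaged people is useful if it shows whom clinicians chose to scan. Here, people referred in 2007 or in 2022–2024 would rarely have a linked scan, whatever the clinical decision. Pooling them with in-window people who were not scanned makes referral date part of the contrast.

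Two distortions can follow. Any characteristic whose recording or case-mix changed over calendar time will differ between the groups. Any variable that keeps accruing after index will also be recorded less often among the latest referrals, who have had little time.

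This matters because only about a quarter of the cohort (5,000 of 20,000) is expected to have scans, yet the callosal angle distributions, the prevalence of imaging features and any accuracy results are described for the memory-service population. A misread check could suggest selection that is absent or mask selection that is present.

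**Working it through.** The article gives no figure for this check, so there is none to reproduce. The calculation below is illustrative.

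**Inputs from Study design:** 20,000 people, 18 referral years (2007–2024), 5,000 imaged, 14 scan years (2008–2021).

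**Assumptions not in the article:** referrals even by year; scans fall in the same period as the referral; imaging is random within the window and absent outside it, so there is no true selection.

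**1. People outside the archive**
- Per year: 20,000 / 18 = 1,111.
- Outside (2007 and 2022–2024): 4 × 1,111 = 4,444, or 22% of the cohort. Of these, 3,333 were referred in 2022–2024.
- Non-imaged: 20,000 − 5,000 = 15,000. Out-of-window share: 4,444 / 15,000 = 30%. For 2022–2024 alone: 3,333 / 15,000 = 22%.
- Imaged share: 5,000 / 20,000 = 25% overall, but 5,000 / 15,556 = 32% within the window.
- With referrals falling 3% a year up to growing 5% a year, the out-of-window share of the non-imaged runs from 27% to 36%, and the 2022–2024 share from 17% to 31%.

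**2. Potential follow-up from referral** (mid-year referral, to the end of 2024, before censoring by death or NPH)
- In-window years run from 16.5 down to 3.5, mean 10.0. This is the imaged mean.
- Non-imaged: (10,556 × 10.0 + 1,111 × 17.5 + 3,333 × 1.5) / 15,000 = 8.7 years.

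**3. Covariates fixed near index (calendar trend only)**

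Let prevalence rise linearly from 30% in 2007.
- To 40% by 2024: 34.4% of imaged against 35.2% of non-imaged, odds ratio 0.97.
- To 50% by 2024: 38.8% against 40.4%, odds ratio 0.94.
- Over the three referral patterns the range is 0.91 to 0.98.

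**4. Variables that accrue after index**

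With event hazard h, death hazard d and potential follow-up t, the chance of being recorded is h/(h+d) × (1 − exp(−(h+d)t)), averaged over referral years.
- h = 0.10, d = 0: 60.1% of imaged against 51.5% of non-imaged. Odds ratio (0.601/0.399) / (0.515/0.485) = 1.42.
- h = 0.10, d = 0.10: 40.8% against 35.1%, odds ratio 1.28.
- With h from 0.02 to 0.20, d of 0 or 0.10, and the three referral patterns, the range is 1.12 to 2.22.

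**5. Restricting to referrals in 2008–2021**

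Every odds ratio in steps 3 and 4 becomes 1.00. This follows from assuming a constant chance of imaging within the window. If that chance changed from year to year, restriction alone would leave some calendar effect, which is why referral year also belongs in the model.

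**The case against.** The strongest reply is that the sentence promises only a comparison on EHR data. A reader might infer that NPH, dementia, death and hospitalisation will be compared by scan status and must differ by construction. The article does not say that. The parallel check on segmentation failures, under Validation of automated CA measure, gives demographics and primary diagnosis as its examples, and most Table 2 covariates are fixed at or near index. For those, unequal follow-up hardly matters. Even NPH symptoms and depression would be protected if the covariate window in Study design overrides the open-ended wording in Table 2. This stands, and it confines the follow-up problem to variables that accrue after index, if they are used.

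A reader might also set 3–16 years of follow-up in scanned people against 0–3 years in the non-imaged. That ignores censoring at death and incident NPH, starts the clock at the scan for one group and at referral for the other, and compares a whole group with a subgroup. Like for like, the means are 10.0 and 8.7 years.

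Other points hold in part:
- The covariates are headed as possible ones and an article condenses the plan, so referral year may yet enter the model. The comparison population, however, is stated, and it is the whole cohort.
- A scan can precede or follow referral by some time, so out-of-window people would rarely, not never, have one.
- The datasets are live and the archive may be extended, but no later date is given.
- Strengths and limitations promises a general look at group differences, so this is not the only safeguard. It is the only specific comparison of imaged with non-imaged people.
- A whole-cohort comparison properly answers whether the imaged subset resembles all 2007–2024 referrals. It should be kept.

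**Conclusion.** The concern holds in limited form. The two date ranges and the whole-cohort comparison are all in the article, and together they make the check a mixture of archive coverage and clinical selection. Under even referral about 22% of the cohort and 30% of the non-imaged are affected; the latter share is 27% to 36% under the other referral trends tried. Yearly referral counts are not given, so these are illustrations.

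The consequence depends on the variable. For covariates closed near index the artefact looks small (odds ratios 0.91 to 0.98). For ever-recorded symptoms or depression, or NPH diagnosis, it could be material (1.12 to 2.22), but those values rest wholly on assumed event and death rates. The documents do not support saying that the comparison is invalid, or that outcomes will necessarily be compared over unequal follow-up. The study is mainly descriptive, and the check can be put right before analysis without new data.

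**What to change.** In Descriptive analyses, make two comparisons in place of one.

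1. **Selection into imaging:** restrict to people referred within the scan-archive window, 2008–2021 or the archive dates at extraction. This drops 2007 as well as 2022–2024. Include referral year in the logistic model, and use only characteristics recorded by a fixed time after referral, so that symptoms, depression and NPH diagnosis are not counted over unequal follow-up.
2. **Representativeness:** keep the whole-cohort comparison, labelled as a description of how the imaged subset differs from all 2007–2024 referrals.

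Also state the referral window to which the prevalence of imaging features applies. The full 2007–2024 cohort can stay for the prevalence of recorded NPH.

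The cost is a few sentences, one extra analysis and fewer non-imaged people in the selection check: about 10,556 rather than 15,000 under even referral.

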### Diagnostic accuracy of CA

We will compare mean or median CA between people with a diagnosis of NPH and other diagnoses, such as dementia and its subtypes, in particular AD, using a two-sample t-test or Mann-Whitney U test.

We will analyse the association between NPH imaging features and NPH diagnosis using logistic regression. If we have sufficient numbers, we will consider using area under the curve (AUC) analysis, and Cox regression for time-to-event analysis. We will consider penalised Cox regression if the number of outcome events is small, as we expect.

If we have enough cases, we will calculate the sensitivity, specificity, positive, and negative predictive values for identifying recorded NPH in this population using CA. Estimated numbers for this are in
Table 3.

**Table 3. T3:** Expected values of cases of NPH picked up on screening in CRIS (based on initial searches undertaken in March 2022). Based on total population of 5,000 individual patient scans and an expected prevalence of approximately 1% of dementia cases
^
71
^. Figures are based on previous sensitivity (97%) and specificity (88%) measures using a cut-off of <90 degrees
^
31
^.

True iNPH cases				
Callosal angle <90		+	-	Totals
	+	49	582	631
	-	1	4268	4269
	Totals	50	4850	5000

